## Abstract

Parkinson’s disease (PD) is characterized by the progressive dopaminergic neuron degeneration, resulting in striatal dopamine deficiency. Mitochondrial dysfunction and oxidative stress are associated with PD pathogenesis. Physical activity (PA) has been shown to ameliorate neurological impairments and to impede age-related neuronal loss. In addition, skin fibroblasts have been identified as surrogate indicators of pathogenic processes correlating with clinical measures. The PARKEX study aims to compare the effects of two different PA programs, analyzing the impact on mitochondrial function in patients’ skin fibroblasts as biomarkers for disease status and metabolic improvement. Early-stage PD patients (n = 24, H&Y stage I to III) will be randomized into three age- and sex-matched groups. Group 1 (n = 8) will undergo basic physical training (BPT) emphasizing strength and resistance. Group 2 (n = 8) will undergo BPT combined with functional exercises (BPTFE), targeting the sensorimotor pathways that are most affected in PD (proprioception-balance-coordination) together with cognitive and motor training (Dual task training). Group 3 (n = 8) will serve as control (sedentary group; Sed). Participants will perform three sessions per week for 12 weeks. Assessment of motor function, quality of life, sleep quality, cognitive aspects and humor will be conducted pre- and post-intervention. Patient skin fibroblasts will be collected before and after the intervention and characterized in terms of metabolic remodeling and mitochondrial bioenergetics. Ethical approval has been given to commence this study. This trial is registered at clinicaltrials.gov (NCT05963425).

**Trial registration.**
https://classic.clinicaltrials.gov/ct2/history/NCT05963425.

## Introduction

Parkinson’s disease (PD) is a disorder characterized by the progressive degeneration of dopaminergic neurons resulting in a deficiency of dopamine in the *striatum* in the basal ganglia [1]. PD patients experience both motor and non-motor symptoms, including anxiety, depression, sleep and gastrointestinal alterations, among others. The motor symptoms typically manifest gradually, initially asymmetrical and later bilateral. The most common primary motor symptoms include *akinesia* (lack of spontaneous voluntary movement), *bradykinesia* (slowness of movement), resting tremor (hands, arms, legs, jaw, and face), rigidity (arms, legs, and trunk), and postural instability. Additionally, people with PD may experience difficulties with balance and coordination [2]. Although the exact mechanism behind the neurodegeneration of dopaminergic cells remains uncertain, current understanding suggests an interaction between genetic and environmental factors as contributors [3,4].

Physical activity (PA) has a very important role and exerts a significant impact in patients with PD. Numerous evidence point to the remodeling and neuroplastic power of PA, including the role of muscle secretory activity in neurodegenerative diseases [5]. Further, PA may be responsible for both systemic [5,6] and neural [7,8] plasticity, defining the concept of *neural systemic dual plasticity* (NSDP) [9]. In the design of this protocol, we aim to determine the effect of exercise at the cellular and molecular level and having as its epicenter mitochondrial function related to changes in gene expression and functionality of mitochondria [10,11]. During PA, a number of myokines and metabolites are released into the bloodstream, many of which can cross the blood-brain barrier (BBB) and exert effects on the central nervous system, in this case the effects of exercise at the systemic level begin as secondary plasticity, that follow different signaling pathways and by passing the BBB has the potential to become primary plasticity [9].

Research has demonstrated that PA not only prevents cognitive decline and the risk of dementia in older adults [12] and other neurodegenerative diseases [13,14] but also mitigates motor deficits, increases new neuron formation, ameliorates neurological impairments, and helps counteract age-related neuronal loss [15]. Further, recent studies have indicated that intensive and cognitively demanding programs are capable of inducing plastic brain changes in individuals with PD [16]. PA plays a crucial role in modulating cortical activity among patients with PD [17]. It has been described that the activation of cortical areas during PA can be attributed to the increased intracerebral blood flow induced by exercise. A study evaluated the motor symptoms of PD using the Unified Parkinson’s Disease Rating Scale-III (UPDRS-III) and compared three groups of patients. Two groups participated in different PA programs, while the third group underwent physiotherapy. Remarkably, both PA groups exhibited a significant improvement of 27.5% in motor symptoms as assessed by UPDRS-III pre and post intervention, whereas the physiotherapy group showed a modest improvement of 2.9%. Notably, all the three groups demonstrated enhanced functional capacity at the end of the intervention [18]. These findings underscore the substantial benefits of PA in ameliorating motor symptoms and enhancing functional outcomes in individuals with PD. On the other hand, the relationship of PA with specific neurological benefits [19], highlights that PA activates a series of processes responsible for maintaining and protecting nerve cells, a phenomenon often referred to as physiological neuroprotection systems. PA favors the production of compensation mechanisms through a reorganization of damaged neural circuits [20].

In healthy subjects, the beneficial effects induced by PA are mediated by improved mitochondrial function and mitophagy [21]. This is relevant, since mitochondrial dysfunction is a key phenomenon associated with early PD, which occurs before the onset of motor symptoms [22]. PA has been shown to improve mitochondrial respiration, thereby affecting adenosine triphosphate (ATP) production and overall mitochondrial function. Indeed, both acute exercise and resistance exercise increase breathing and respiratory control index [23,24].

Moreover, skin fibroblasts from patients with PD have emerged as a valuable resource for studying this neurodegenerative disorder and identifying potential biomarkers [25]. Since acquiring human brain samples is only feasible *postmortem*, several researchers have turned to the easily accessible peripheral samples, such as skin fibroblasts. These studies emphasize that fibroblasts, originating from the same genetic lineage as neurons [26], can serve as reliable indicators of cumulative cellular damage related to the age and patient-specific habits [27]. The relevance of skin fibroblasts as a surrogate model in this research lies in their ability to mirror specific cellular deficiencies commonly observed in nigral neurons. These deficits serve as indicators the neurodegenerative process of PD and can be detected in fibroblasts from PD patients [27]. Hence the importance of fibroblasts as a surrogate model for physiopathological processes, as it would allow mitochondrial function to be correlated with clinical measures, such as motor function by means of the MDS-UPDRS III scale [28]. Our recent studies examining skin fibroblasts from PD patients have revealed metabolic and mitochondrial abnormalities [23], establishing a clear link between mitochondrial dysfunction in skin fibroblasts samples from PD patients and PD pathogenesis. These investigations demonstrated decreased oxygen consumption rate (OCR), proton leak, maximal respiration, respiratory replacement capacity, and OCR-linked ATP levels in skin fibroblasts from patients with PD, providing clear evidence of compromised mitochondrial function.

The aim of this clinical study is to explore the impact of PA on metabolic remodeling, utilizing a less invasive model to investigate PD and its pathogenic mechanisms. Specifically, the study aims to examine fibroblasts derived from PD patients, which serve as an accessible and informative model to gain insights into the underlying deficits affecting neurons. By investigating the beneficial mechanisms associated with PA and studying the pathophysiological alterations within fibroblasts, this research holds the potential to deepen our understanding of PD and facilitate the development of novel diagnostic tools, and revolutionary therapeutic interventions applicable to clinical practice.

## Methods and analysis

### Study design

PARKEX trial is a randomized clinical trial with an open design (registered at clinicaltrials.gov; NCT05963425). It is a non-pharmacologically interventional study, with a total of twenty-four patients. Screening and assessment visits are occurring in both neurology and PA laboratory settings.

A SPIRIT schedule and overview of the study design can be found in Figs 1 and 2.

**Fig 1 pone.0293774.g001:**
[figure not shown]
SPIRIT schedule of enrolment, interventions, and assessments for the PARKEX study.

**Fig 2 pone.0293774.g002:**
[figure not shown]
Comprehensive overview of the PARKEX study design.

This protocol has been developed following the Standard Protocol Items: Recommendations for Interventional Trials (SPIRIT) checklist (see S1 Fig) [29].

### Subject recruitment

Participants for the study will be recruited by the Grup de Malalties Neurodegeneratives of the Vall d’Hebron Institut de Recerca (VHIR), Barcelona, Spain. To ensure the minimum required sample size of 24 patients, as stipulated in the project, the VHIR researchers will leverage their connections with the Catalan Parkinson’s Association and other Movement Disorders Units in prominent hospitals across the state. Participants who meet the inclusion criteria and sign the informed consent will be recruited and randomized.

### Sample size calculation

The sample size for this study was determined using the GRANMO program with the model of observed proportions with respect to a reference. For the calculation it has been taken into account that the "maximal respiration” is the key indicator to determine the effects of PA on mitochondrial function, because the entire respiratory chain is forced to the maximum. The calculation has been made accepting an **α** risk of 0.05 and a beta risk of less than 0.2 in a two-sided contrast. Based on preliminary data, there is a difference of "maximal respiration" equal to or greater than 0.263 units [23]. It is assumed that the proportion in the reference group is 0.019 in people older than 50 years [30]. Being an interventional study, the percentage of necessary replacements has been predicted to be 20%.

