### Intervention

Two different programs are designed in order to investigate the effect of PA on mitochondrial function in skin fibroblasts of patients with PD.

The first group (n = 8) will undergo basic physical training (BPT) focused on strength and resistance. The second group will engage in BPT combined with functional exercises (BPTFE), which includes cognitive and dual task training. A third group, the sedentary group, will serve as the control. The intervention in the two PA programs will last 3 months.

The interventions will be conducted in group settings, with 8 patients per group, and each session will last for 60 minutes. The frequency of the sessions will be 3 times a week. The intervention programs will be structured into 3 meso-cycles of 4 weeks. During the initial two weeks, the workloads will be maintained to facilitate the adaptation period. For the BPTFE program, in addition to adapting to the load, participants will also need to adapt to complex motor execution tasks. Starting from the third week, the workload will progressively increase.

In both PA programs, exercises will target the large muscle groups, with a component/emphasis on the eccentric phase of concentration. The *kBox4* Platform, a device designed to maximize performance and training outcomes, will be used to enhance the eccentric phase of the exercises. This device, provided by Exxentric AB (Stockholm, Sweden), a company specialized in innovative and evidence-based training equipment and methods, will be loaned for the study. *kBox4* is controlled by a specific program, *Kmeter*, which records and stores all the information (duration, intensity, repetitions, etc.) of each movement. Exxentric *kBox4* will be adapted with special harnesses, insurances on the wall and in front of support bars, according to the needs of the patients. In addition to the major muscle groups, specific attention will be given to the key muscles involved in the gait cycle, such as the tibialis anterior, medial gastrocnemius, rectus femoris, and hamstrings, from a biomechanical perspective. This aspect will be common to both programs, with the only difference being that the BPT program will have a greater workload due to the division of activity time between functional exercises and Dual Task Training in the BPTFE program.

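### The sample size rests on a one-sample proportion test, so the stated power is not established for any between-arm comparison of maximal respiration

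*Protocol article*

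**What the plan says.** Under Sample size calculation, the protocol article states that the size was "determined using the GRANMO program with the model of observed proportions with respect to a reference". It takes maximal respiration as the key indicator and sets the error rates as an alpha "risk of 0.05 and a beta risk of less than 0.2 in a two-sided contrast". Preliminary data are said to show a difference in maximal respiration "equal to or greater than 0.263 units". The reference value is given in these words: "It is assumed that the proportion in the reference group is 0.019 in people older than 50 years". For losses, "the percentage of necessary replacements has been predicted to be 20" percent. The section prints no resulting n and does not say whether the result is per arm or in total.

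The size appears elsewhere. Subject recruitment treats 24 as a requirement ("To ensure the minimum required sample size of 24 patients"), and the Abstract and the Intervention section use three groups of 8 ("The interventions will be conducted in group settings, with 8 patients per group").

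Table 2 makes maximal respiration the named primary measure, with oxygen consumption rate determined on a Seahorse analyser. Randomization describes two exercise groups and a control group. Statistical analysis plans a mixed model for repeated measures to find which type of intervention does most good, and the Discussion promises a comparison of BPT with BPTFE.

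**The concern.** The named model tests the proportion observed in a single group against a known constant. The trial does something different in two respects.

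- **Outcome.** Oxygen consumption is continuous, and the article defines no responder that would turn it into a proportion. A difference expressed in respiration units is paired with a reference expressed as a proportion. A proportion model takes no standard deviation, yet the power to compare means depends on one.
- **Comparison.** The control group is randomised and has its own sampling error. A one-sample model treats the comparator as known exactly, so it asks for far fewer patients.

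At stake is how the results will be read. With a stated beta below 0.2 and 24 presented as the number required, a reader could take a null between-arm result as an adequately powered negative. The calculation gives no ground for that.

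**Working it through.** **Inputs** (Sample size calculation, unless noted): p0 = 0.019; d = 0.263; so p1 = 0.019 + 0.263 = 0.282; two-sided alpha 0.05 (z = 1.96); power 80% (z = 0.8416); 20% for losses; 8 per arm and 24 in total (Abstract, Subject recruitment, Intervention). No SD is given.

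**1. Reproducing the plan's figure**

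One proportion against a fixed reference:

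n = [1.96·√(p0(1−p0)) + 0.8416·√(p1(1−p1))]² / d²

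= [1.96·√(0.019·0.981) + 0.8416·√(0.282·0.718)]² / 0.263²

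= (0.2676 + 0.3787)² / 0.06917 = 6.04

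With 20% loss: 6.04 / 0.8 = 7.55, so 8; and 3 × 8 = 24. Rounding 6.04 up to 7 first gives 7 / 0.8 = 8.75, so 9. The match with the design is therefore good but depends on the order of rounding.

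**2. Same proportions, two arms**

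With the mean proportion (0.019 + 0.282)/2 = 0.1505:

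n per arm = [1.96·√(2·0.1505·0.8495) + 0.8416·√(0.019·0.981 + 0.282·0.718)]² / 0.263²

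= (0.9911 + 0.3958)² / 0.06917 = 27.8, so 28 evaluable; 27.8 / 0.8 = 34.8, so 35 with 20% loss.

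Power at 8 per arm: Φ[(0.263·√8 − 0.9911)/0.4702] = Φ(−0.526) = 0.30.

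The normal approximation is rough here, since the expected count in the reference arm is 8 × 0.019 = 0.15. The step shows only how much the one-sample model saves by leaving out the second arm. It is not a proposal to analyse a binary outcome.

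**3. Continuous outcome, two arms**

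Two-sample t-test (noncentral t), one pairwise contrast, two-sided 0.05, no baseline adjustment. SD means the SD of whatever is analysed.

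| Evaluable per arm | Difference for 80% power | Largest SD at which 0.263 units has 80% power | 95% CI half-width |
|---|---|---|---|
| 8 | 1.51 SD | 0.263/1.507 = 0.175 | 2.145·√(2/8) = 1.07 SD |
| 6 | 1.80 SD | 0.263/1.796 = 0.146 | 2.228·√(2/6) = 1.29 SD |

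If alpha were divided by 3 for three pairwise contrasts, the detectable differences would be 1.81 SD and 2.19 SD.

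The row for 6 applies only if the 20% is attrition that is not made good (8 × 0.8 = 6.4).

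**4. Range over an assumed SD, for a difference of 0.263 units**

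n per arm = 2·(1.96 + 0.8416)²·(SD/0.263)², before dropout; power from the t-test.

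| Assumed SD (units) | n per arm | Power, 8 per arm | Power, 6 per arm |
|---|---|---|---|
| 0.15 | 6 | 90% | 78% |
| 0.20 | 10 | 69% | 54% |
| 0.263 | 16 | 46% | 35% |
| 0.40 | 37 | 23% | 18% |
| 0.526 | 63 | 15% | 12% |

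The result turns on a quantity that the plan's model does not use.

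**The case against.** The strongest reply is that nothing here shows the trial to be underpowered. That stands. A reader might infer that 80% power does not exist for these comparisons, but without an SD the true power cannot be computed. With an SD of about 0.175 units or less, 8 per arm would reach 80% for one unadjusted contrast.

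Baseline would help too. Biopsies are taken before and after the intervention and a repeated-measures model is planned. Under an assumed pre-post correlation r, adjustment multiplies the detectable difference by about √(1−r²): 1.51 SD falls to about 1.31 SD at r = 0.5 and 1.08 SD at r = 0.7. The article gives no correlation, so this is a possibility and not a rebuttal.

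Three further readings are tempting and go beyond the text:

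- *The 24 is three one-sample studies side by side.* The arithmetic fits, but the article prints no n, and another rounding order gives 9 per arm.
- *Only about 6 evaluable patients per arm are planned.* The article speaks of replacements, which could also mean that dropouts are replaced.
- *The 0.263 and the 0.019 cannot share a scale.* The wording mixes units and a proportion, but what each figure measures lies in cited sources not at hand.

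It could also be said that a journal article condenses the full protocol. That does not help. The article names the model, and the model is one-sample and binary. This is a wrong statement, not an omitted detail.

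**Conclusion.** The concern holds in this form: the calculation as published does not establish a beta below 0.2 for exercise versus control or for BPT versus BPTFE. That conclusion needs only the article's description of its model, its primary measure and its three randomised arms. It does not depend on the rounding or on the meaning of the 20%.

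The size of the gap is conditional. On the plan's own proportions, about 28 evaluable per arm would be needed against 8 planned, with about 30% power at 8. On a continuous scale, for one unadjusted contrast and without baseline adjustment, 80% power needs about 1.5 SD at 8 per arm, or about 1.8 SD if 6 remain. Whether 0.263 units is that large relative to the SD cannot be told from the article.

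**What to change.** Keep the 24 patients; Trial status reports that recruitment has started. Rewrite the Sample size calculation paragraph:

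1. Withdraw the proportion model and the 80% power claim for the between-arm comparisons, and state that the published calculation does not cover them.
2. Report the detectable difference and the 95% confidence-interval half-width for the between-arm contrast in change in maximal respiration. Use the SD from the preliminary fibroblast data and the pre-post correlation if available, and give the results in the units of the assay.
3. Say whether the 20% is inflation for loss or replacement of dropouts. Give the figures at 8 per arm and, if it is loss, also at 6.

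The rewrite should not call 24 a feasibility number or say that dropouts are not replaced unless the sponsor confirms it, because the article supports neither statement.

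The cost is one paragraph and no extra patients. The downside is that the stated power becomes less favourable. If the preliminary SD proves small enough, a power statement can be made again on the right basis.

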### Eligibility criteria

To be included in this study, subjects must meet specific criteria. These criteria include having a medical diagnosis of idiopathic PD, falling within stages of I-III on the H&Y scale in the ‘on’ phase, and demonstrating a good cognitive status with a score 26 or higher on the Montreal Cognitive Assessment (MoCA). Participants must be between 50 and 70 years old and capable of walking independently for at least six minutes. In addition, it is important that the subjects have not made any changes to their medication regimen in the last month. The International Physical Activity Questionnaires (IPAQ) will be used to normalize the groups based on the basal levels of PA [31]. Once the subjects are selected, they will receive a detailed explanation of the research procedures, and the subjects will voluntarily express their consent to participate in this study, signing the informed consent.

Certain criteria will lead to the exclusion of subjects from participation in this study. These criteria encompass the presence of any pathology other than idiopathic PD, cognitive impairment with a MoCA score below 26 points, uncontrolled cardiovascular disease, diabetes, visual impairment, or recent musculoskeletal disorders in the upper or lower extremities that may interfere with balance and locomotion. Additionally, individuals currently undergoing another therapeutic exercise protocol or who have undergone surgery aimed at influencing a specific PD symptom will not be eligible to participate.

### Randomization

All patients who provide their consent to participate in the study and fulfil the inclusion criteria will be randomized. A sample block randomization method will be employed, dividing the participants in three groups: two intervention groups and one control group. The allocation of individuals to intervention or control groups will be blind to assessors and participants. An independent investigator, uninvolved in the study, will perform the random assignment of subjects into the three groups. This will be done using a computer-generated random allocation table, stratified based on the PD stages (i.e., according to H&Y classification stages I, II, III), basal physical activity levels, sex, and age.

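### Joint stratification on four factors gives at least 24 strata for 24 patients, so three groups of 8, matched on age and sex, are improbable rather than assured

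*Protocol article*

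**What the plan says.** The Study design section fixes the trial size, "with a total of twenty-four patients". The Randomization section states the method, "A sample block randomization method will be employed, dividing the participants in three groups", and says that the allocation table is computer-generated and "stratified based on the PD stages (i.e., according to H&Y classification stages I, II, III), basal physical activity levels, sex, and age". H&Y stage is the only factor whose levels are listed.

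On activity, the Eligibility criteria say "The International Physical Activity Questionnaires (IPAQ) will be used to normalize the groups based on the basal levels of PA", with no number of categories. On age they say "Participants must be between 50 and 70 years old", with no cut-point. No block size is given, and the text mentions no limit on arm size, no minimisation and no merging of strata.

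Two other places depend on the result of the allocation. The Abstract gives n = 8 for each group and says that patients "will be randomized into three age- and sex-matched groups". The Intervention section says "The interventions will be conducted in group settings, with 8 patients per group".

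**The concern.** Blocking controls arm sizes only where blocks fill up. Each stratum has its own blocks, so each stratum can leave one unfinished, and an unfinished block can favour any arm. With about as many strata as patients, nearly all blocks are unfinished and the chance imbalances add up across strata.

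The stated method therefore works against the two properties that the plan relies on: arms of 8, for which the training classes are designed, and arms alike in age and sex. With 8 patients per arm, an excess of two or three men or older patients in one arm is hard to separate from an effect of training on fibroblast respiration.

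**Working it through.** **The plan's own figure.** The sample size section gives a reference proportion of 0.019, a difference of 0.263, two-sided alpha 0.05, beta 0.2 and 20% replacements. A one-sample proportion formula gives

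n = [1.960 × √(0.019 × 0.981) + 0.842 × √(0.282 × 0.718)]² / 0.263² = 6.04.

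Then 6.04 / 0.8 = 7.55, rounded up to 8 per group, and 3 × 8 = 24. So 24 can be reproduced. Whether that formula suits the outcome is a separate matter.

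**Number of strata.** H&Y 3 and sex 2 are given. Activity and age need at least two levels each to be stratification factors.
- Lowest count: 3 × 2 × 2 × 2 = 24 strata, or 24/24 = 1.0 patient per stratum.
- With three activity levels and two age bands (both assumed): 3 × 3 × 2 × 2 = 36 strata, or 24/36 = 0.67 patients per stratum.
- Smallest 1:1:1 block: 3 patients.

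**Arm sizes.** Simulation, 6,000 runs per scenario, 24 patients entering one at a time, separate permuted blocks in each stratum. The assumed skewed mix is H&Y 25/55/20%, activity 30/50/20% (50/50% with two levels), sex 60/40%, age 40/60%. The strongly skewed mix is 10/80/10, 20/60/20, 65/35 and 30/70%.

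| Scheme | 8/8/8 | Gap of 3 or more | Smallest arm 6 or fewer |
|---|---|---|---|
| 36 strata, even mix, blocks of 3 | 5.1% | 70% | 62% |
| 36 strata, skewed, blocks of 3 | 5.3% | 67% | 58% |
| 36 strata, strongly skewed, blocks of 3 | 8.6% | 57% | 46% |
| 36 strata, even mix, blocks of 6 | 3.6% | 77% | 69% |
| 24 strata, even mix, blocks of 3 | 5.6% | 66% | 57% |
| 24 strata, skewed, blocks of 3 | 6.8% | 62% | 52% |
| H&Y only, blocks of 3, skewed | 38% | 2.6% | 1.5% |
| Unstratified blocks of 3 | 100% | 0% | 0% |
| Simple randomisation | 3.3–3.6% | 78–80% | 70–74% |

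The last row can be checked exactly: 24!/(8!)³ / 3²⁴ = 9,465,511,770 / 282,429,536,481 = 3.4%. In the first row about 17.7 strata are occupied, 12.5 of them by a single patient, and about 3 of the 24 patients are in a completed block. A repeat of the simulation put the gap of 3 or more at 67 to 72%.

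**Balance on the factors.** Mean difference between the largest and smallest arm within a factor level, in patients (even mix, 36 strata, blocks of 3):

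| Factor | Four-factor strata | Unstratified blocks | Simple |
|---|---|---|---|
| H&Y | 2.26 | 2.20 | 2.70 |
| Activity | 2.26 | 2.21 | 2.70 |
| Sex | 2.79 | 2.34 | 3.34 |
| Age | 2.81 | 2.36 | 3.32 |

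With 24 strata (even mix) H&Y is slightly better under the four-factor scheme (2.05 against 2.21), but sex (2.53 against 2.36) and age (2.56 against 2.38) are still worse. For the worst level of each factor the mean imbalance is 3.2–3.5 patients with four-factor strata, 2.5–2.7 with unstratified blocks, and about 1.5–1.7 with minimisation limited to 8 per arm. The last scheme gives 8/8/8 in every run.

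**Precision.** The standard error of a pairwise difference is proportional to √(1/n₁ + 1/n₂). For 8 against 8 this is √0.25 = 0.500; for 6 against 9 it is √(0.1667 + 0.1111) = 0.527, which is 5% larger. Averaged over the simulated arm sizes the increase is about 3%.

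**The case against.** **Implementation is not fixed.** The article condenses a fuller protocol and need not give block size, cut-points or a limit per arm. Nor does it say that patients are allocated one by one. Recruitment was expected to run only from mid-September to October 2023. If all 24 were enrolled first, sorted by the four factors and allocated in blocks of 3 down the list, 8/8/8 would be certain and the mean imbalance per factor level would fall to about 1.6–1.7 patients. This stands as a limit: the text neither states nor excludes that procedure. It does not remove the point, because stratified blocks in their usual form conflict with the fixed groups.

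**What a reader might infer, and should not.**
- That 8 per arm and balance cannot be achieved. An 8/8/8 split still arises by chance in about 4 to 9% of runs, and factor balance is better than under simple randomisation.
- That the comparison is badly weakened or biased. Allocation remains random, and the average loss of precision is about 3% in standard error.
- That there are 36 strata. The document supports only a lowest count of 24.
- That classes cannot run with other than 8. The Intervention section gives no minimum or maximum, and the sample size allows for 20% replacements.

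**The remedy has a cost.** A limit of 8 makes the last allocation certain, and more than one if an arm fills early. In an open trial that matters. This also stands, and the fix provides for it.

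**Conclusion.** The concern holds in this limited form. As written, the scheme makes three arms of 8, matched on age and sex, improbable. With blocks of 3 and an even or moderately skewed patient mix, 8/8/8 arises in about 5 to 7% of randomisations and arm sizes differ by 3 or more in about 62 to 72%. A strongly skewed mix is kinder (8.6% and 57%); blocks of 6 are worse. Stratifying on all four factors gives up the arm-size control of plain blocks and gains no overall balance over them.

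The result assumes one-by-one allocation from a separate list per stratum, at least two levels for activity and for age, and the patient mixes shown. It does not depend on whether there are 24 or 36 strata. What is at stake is chiefly prognostic balance and the planned classes, not power.

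**What to change.** For patients not yet randomised, replace the four-factor stratified blocks with minimisation on the same four factors, with a random element (for example, probability 0.8 for the arm that gives the best balance) and a limit of 8 per arm. The independent investigator already named for the task can run it, entering patients already allocated as starting counts. State the activity categories and age cut-point used.

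The cost is a short script, a brief amendment and a little more work for that investigator. Because the limit makes the final allocation or allocations predictable, keep the running counts from staff who recruit.

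If minimisation is not available, use unstratified permuted blocks of 3, which secure 8/8/8 once all 24 are randomised. Alternatively, use blocks stratified by one factor only. With H&Y alone these give exactly 8/8/8 in only 38% of runs, but a gap of 3 or more in only 2.6%. In either case do not describe the arms as matched on age and sex.

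Recruitment was due to finish by October 2023. If all patients have been allocated, what remains is to report the achieved arm sizes and the distribution of the four factors by arm, and to drop the claim of matching unless the data bear it out.
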